## 9.0 MONITORING OF PATIENTS

### 9.1 Table of Required Observations

|                                         | Baseline | Cycle 1,
week 2 | Pre Odd
cycles | Pre Even
Cycles | Off Treatment
(w/in 7 days of
last dose) |
|-----------------------------------------|----------|--------------------|-------------------|--------------------|------------------------------------------------|
| AE Evaluation                           |          |                    | 4                 | 4                  | 7,12                                           |
| MRI                                     | 1        |                    | 11                |                    | 13                                             |
| H&P, Neuro exam                         | 1        |                    | 11                | 11                 | 7                                              |
| Minimental                              | 1        |                    |                   |                    |                                                |
| KPS                                     | 1        |                    | 11                |                    | 7                                              |
| Vital Signs                             | 1,5,6    |                    | 11,6              | 11,6               | 6,7                                            |
| Hematology                              | 1,9      |                    | 4,8,9             | 4,8,9              | 7,9                                            |
| Serum Chemistry                         | 1,10     |                    | 4,10              | 4,10               | 7,10                                           |
| LDH level                               | 1        |                    | 4                 | 4                  | 7                                              |
| Serum Troponin Level                    | 1        |                    | 2,14              | 2,14               | 15                                             |
| Serum Pregnancy Test                    | 1        |                    |                   |                    |                                                |
| Laboratory correlative
tissue sample | 1,3      |                    |                   |                    |                                                |
| 12-lead ECG                             | 1        |                    |                   |                    |                                                |
| Serum Biomarkers                        | 16       | 16                 |                   |                    |                                                |

- 1 – All baseline measurements must be done within 14 calendar days prior to start of treatment administration unless otherwise specified.
- 2 – See section 5.1 for guidelines for elevated serum troponin.
- 3 – Archived Tissue to be obtained and sent unstained paraffin-embedded tissue (from the most recent tumor block available).  
Investigators should make efforts to collect and ship one block or 15-20 slides. See Section 9.5 for details.
- 4 – within -3 days
- 5 – Height should be obtained at baseline
- 6 – Vital signs include temperature, blood pressure, respiratory rate, and heart rate (weight only needs to be obtained every odd cycle)
- 7 – Repeat only if > 3 calendar days since last eval/test
- 8 – If ANC < 1500 or plts < 100,000, CBCs/differentials will be repeated twice a week until counts are recovered (ANC ≥1500 or plts ≥100,000) per protocol. If counts are recovered (ANC ≥1500 or plts ≥100,000) on day of scheduled drawing do not repeat till next protocol schedule day.
- 9 – CBC with differential count and platelet count
- 10 – Na, K, HCO3, Ca, glucose, BUN, creatinine, total bilirubin, SGOT, SGPT, alkaline phosphatase, albumin, GGT, total protein
- 11 – within -5 calendar days (MRI should be obtained and evaluated prior to start of new cycle)
- 12 – Collect for at least 30 days post last dose of AT-101. Patients who are discontinued due to an AE will be followed until AE resolves.
- 13 – repeat only if > 14 days since date of last scan
- 14 – Needs to be drawn after the last dose of AT-101 in each treatment cycle
- 15 – Needs to be drawn the last day of treatment
- 16 – Serum Biomarkers are being collected within 24 hours before the first dose of AT-101 and after one week of therapy (any time during week 2 of cycle 1). See Section 9.5.2 for details.

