In the initial Phase 1 trial, DLTs were reversible grade 4 elevated ALT/AST at daily doses >40 mg/day (Saleh *et al.*, 2005). The principal AEs seen with daily dosing include grade 1 nausea, diarrhea, and fatigue, but one of six patients receiving 40 mg AT-101 daily experienced grade 4 hypokalemia and grade 3 nausea. Stable measurable disease and a reduction in circulating lymphocytes from about 33,000/dL to 22,000/dL were reported in one patient with CLL after 5 cycles at 10 mg AT-101 daily. Of interest, this patient's lymphocyte count consistently rose during the week off therapy, then decreased once AT-101 was restarted. Other evidence of efficacy has been provided by three patients with non-small cell lung cancer (NSCLC) who remained on study with stable disease (SD) for more than 72 to 123 days; in addition, SD (66+ days) has been reported in a patient with a parotid tumor treated at 40 mg daily AT-101.

Additional Clinical Studies with AT-101

AT-101 is being investigated in several Phase 1-2a clinical trials as a single agent or in combination with standard agents for the treatment of patients with advanced solid tumors, lymphoma, or chronic lymphocytic leukemia. As of November, 2006, approximately 155 patients have been enrolled on 8 Phase 1/2 trials. Most patients have received AT-101 once or twice daily, every day for 21 out of every 28 days, in these trials. Total daily AT-101 doses for these patients have been 5-60 mg. The majority of patients have been treated with AT-101 on a daily schedule; however, alternative schedules are currently being tested.

Clinical trials conducted with AT-101 are ongoing; however, preliminary safety data show that the most common AEs, when AT-101 is administered on a once daily schedule, have been gastrointestinal (GI) and grade 1/2 fatigue. The GI AEs include nausea, vomiting, abdominal pain, abdominal discomfort, diarrhea, constipation, and small bowel obstruction (SBO). The most common SAEs reported include nausea, vomiting, SBO, and ileus, especially after several months of continuous dosing. While some of these SAE reports have been unrelated to AT-101 administration and attributed to disease progression, the majority have been related to AT-101 and have resulted in the hospitalization of research subjects. Reversible elevation of ALT and AST were dose-limiting at doses greater than 40 mg/day, administered daily for 21/28 days, in the initial Phase 1 trial.

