## A Phase 2 Study of R-(-)-gossypol (Ascenta's AT-101) in Recurrent Glioblastoma Multiforme

NABTT #: 0702

NCI #: NABTT 0702

Principal Investigator: [name]

isolated elevations of troponin to 0.3-0.8 ng/mL (upper limit of normal, 0.2 ng/mL). One of these patients had a single elevation of serum troponin after one week of AT-101 at 50 mg/day, with no associated cardiac findings, and continued to receive AT-101 for one complete cycle with no reported cardiac AEs and with normalization of the troponin level. The three other elevations were not considered clinically significant by the investigator. These patients did not have cardiac related clinical findings, and the troponin levels were found to be normal upon repeat testing within one week later.

ECGs were performed on all patients prior to enrollment and weekly during the treatment period with AT-101 on the initial Phase 1 study and each month on subsequent studies. The ECGs were assessed as either normal, abnormal but not clinically significant, or abnormal but clinically significant with comments by the investigator. As of 31 July 2006, there have been no reports of QTc prolongation reported as AEs or SAEs.

There have been 13 adverse events categorized for cardiac rhythm abnormalities. Only 3 of these were reported as possibly related to AT-101. Of the 13 reports, 2 were for arrhythmias, 1 was for a ventricular arrhythmia and was possibly related, 1 was for palpitations, 1 was for PAC and was possibly related, 3 were for PVCs with 1 possibly related, 3 were for sinus tachycardia, and 3 were for tachycardia.

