## 4.0 TREATMENT PLAN

### 4.1 Treatment Schema

[figure not shown]

Treatment for this protocol will be administered on an outpatient basis. Each patient will receive 20mg of AT-101 orally every day for 3 weeks (21 days) of each cycle. Each treatment cycle is 28 days. Tumor tissue and blood samples will be obtained from each patient prior to beginning treatment with AT-101 (See section 9.5). Treatment of an individual patient will continue until there is objective or clinical evidence of either disease progression or treatment-related, dose-limiting toxicity, or if the patient decides to discontinue treatment for any reason. All patients will be given drug to take home and a drug calendar that explicitly details how many tablets of AT-101 the patient will be taking each day. The patient will be asked to record the amount of AT-101 actually taken as well as the date and time of each dose in a pill diary.

Prior to starting each treatment cycle the patient must meet the following criteria on Day 1 of each treatment cycle:

- $ANC \geq 1,500/\text{mcL}$
- $\text{Platelets} \geq 100,000/\text{mcL}$
- Non-hematologic toxicity recovered to  $\leq$  grade 1, tolerable grade 2 or pretherapy baseline
- No medical condition or other circumstance (including progressive disease) exists that, in the opinion of the investigator, would make the patient unsuitable for further participation in the study.

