### **11.3 Secondary Objectives**

1. To assess the acute and late toxicities associated with the treatment. The proportion of patients with serious or life threatening toxicities will be estimated along with 95% confidence intervals. The frequency of different type toxicities will be tabulated by each cycle of the treatment.
2. To estimate tumor response rate. The probability of tumor response (definition: section 8.1) will be estimated using binomial distribution along with 95% CI.
3. To estimate a 6-month progression-free survival rate. The 6-month progression-free survival is defined as patient who is alive and disease progression free at the time of 26-week (6 months) from first day of the treatment (definition of disease progression: section 10.0). The probability of 6-month progression-free survival will be estimated using binomial distribution.
4. Correlative study: Apoptosis can be triggered through either the intrinsic (mitochondrial) or extrinsic (receptor) pathways. The study will focus on regulators of both the intrinsic (Bcl-2, Bcl-XL, Mcl-1, Bax, Bak) and extrinsic (FLIP, survivin, XIAP) pathways. Serum will be collected for analysis of apoptotic protein levels immediately before the first dose and after one week of therapy. Every effort will be made to collect tumor tissue before and after treatment. Descriptive statistics will be used to summarize the protein expressions and patient's MGMT methylation status.

The Cox's proportional hazard model will be used to explore the association between change of the proteins and patient's survival status.

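### In continuing cycles, scheduled blood counts and chemistry fall only in the off-drug week, so short-lived laboratory toxicity can be missed and the laboratory part of the toxicity rates may be biased downward

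*Protocol*

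**What the plan says.** Section 4.1 sets the exposure: "Each patient will receive 20mg of AT-101 orally every day for 3 weeks (21 days) of each cycle. Each treatment cycle is 28 days".

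Table 9.1 lists hematology, serum chemistry and LDH at baseline, before odd cycles, before even cycles and at off treatment. The pre-cycle entries carry footnote 4, "4 – within -3 days". The column for cycle 1 week 2 is empty for all three. It contains only the serum biomarker draw, which footnote 16 places "after one week of therapy (any time during week 2 of cycle 1").

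Troponin stands in the same pre-cycle columns, but footnote 14 says "Needs to be drawn after the last dose of AT-101 in each treatment cycle". Section 4.3 agrees with the footnote, and neither gives a latest day.

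Section 11.3 item 1 states the estimate to be made: "The proportion of patients with serious or life threatening toxicities will be estimated along with 95% confidence intervals". It also tabulates toxicities by cycle. Section 11.4 suspends the study for review if, among the first 25 patients with at least one cycle, the lower 95% confidence bound on the grade 3 or higher toxicity rate is above 18%. Section 11.5 makes the go/no-go judgement depend heavily on toxicity.

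**The concern.** Section 9.2.1 counts an abnormal laboratory finding as an adverse event, so laboratory values feed the 11.3 and 11.4 rates. A patient can report last week's nausea at the pre-cycle visit, but nobody can recall last week's transaminase or potassium. An abnormality that appears during dosing, causes no symptoms and resolves in the off-drug week leaves no trace in the scheduled data.

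The protocol gives some reason to think such events exist for this drug. Section 2.0 reports "Reversible elevation of ALT and AST were dose-limiting at doses greater than 40 mg/day, administered daily for 21/28 days", and says of three troponin elevations that "the troponin levels were found to be normal upon repeat testing within one week later". The adverse event list in 9.3 includes raised ALT, raised AST and hypokalemia among expected events.

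Missed laboratory events can only lower the recorded rate. At stake are a stated secondary objective (acute toxicity), the sensitivity of the trial's one planned toxicity check, and the safety side of the decision in 11.5.

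**Working it through.** **Timing.** Inputs from 4.1 and footnote 4: last dose day 21; next cycle starts on day 28 + 1 = 29; window from 3 days before to the start day.

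- Earliest draw: day 29 − 3 = 26, which is 26 − 21 = 5 days after the last dose.
- Latest draw: day 29, which is 29 − 21 = 8 days after the last dose.

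The protocol states no figure for this interval, so there is none to reproduce.

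**Other scheduled tests in Table 9.1.**

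- Off-treatment hematology and chemistry are due within 7 days of the last dose (0 to 7 days), and are repeated only if more than 3 days have passed since the last test. They can fall close to exposure, but only in patients who are stopping.
- Footnote 8 requires twice-weekly counts, but only after a low count has been found.
- Troponin may be drawn from day 21 to about day 29 (0 to 8 days after the last dose) and still comply with footnote 14. At off treatment, footnote 15 asks for the last day of treatment.

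So no hematology or chemistry test is scheduled on a dosing day in a continuing cycle.

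**Trigger of the 11.4 toxicity rule at n = 25.** Exact lower bound for x events: the α quantile of Beta(x, 26 − x), with α = 0.025 (two-sided 95%) or 0.05 (one-sided 95%). Section 11.4 does not say which is meant.

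| x of 25 | Two-sided bound | One-sided bound |
|---|---|---|
| 8 | 14.9% | 17.0% |
| 9 | 17.97% | 20.2% |
| 10 | 21.1% | 23.6% |

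The 18% limit is first exceeded at 10 of 25 (two-sided) or 9 of 25 (one-sided). At 9 of 25 the two-sided bound falls short by 0.03 percentage points, so a single uncounted patient can decide the result.

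**Illustration of sensitivity.** Assumed, not from the protocol: a true grade 3 or higher rate of 40%, and a fraction f of patients with such toxicity who go uncounted. Recorded rate = 0.40 × (1 − f). P(criterion met) is the upper binomial tail with n = 25.

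| f | Recorded rate | 10 of 25 or more | 9 of 25 or more |
|---|---|---|---|
| 0 | 0.40 | 0.575 | 0.726 |
| 10% | 0.36 | 0.410 | 0.575 |
| 25% | 0.30 | 0.189 | 0.323 |

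The table shows how the rule responds to missed events. It does not say how many are missed.

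**Dose-modification rules against the schedule.** Section 5.1 tells sites to skip a dose for grade 4 hematologic toxicity and to hold drug for raised troponin. Those instructions fit values obtained during dosing. The same section bases hematologic adjustments on counts taken in preparation for the treatment day, and 9.1 schedules nothing while the patient is on drug. The sections leave unclear which values the skip and hold rules are meant to act on.

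**The case against.** The pre-cycle timing has a purpose. It serves the day 1 retreatment criteria in 4.1 and the basis for hematologic dose adjustment in 5.1, so the schedule is a choice and not an error. That stands.

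The trial also has other routes to detection. Investigators record adverse events throughout (9.2.2), 5.1.1 prompts a work-up of persistent gastrointestinal symptoms, and tests may be drawn on clinical grounds. The toxicities that dominate the protocol's account are clinical: every event in the over-20% column of the 9.3 list (abdominal pain, diarrhea, nausea, vomiting, fatigue, anorexia) is recognised without a blood test, while ALT, AST, potassium, creatinine and troponin changes sit in the column for 20% or less. This limits the possible size of the bias. It does not recover silent events.

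A reader might infer more: that the toxicity rates are understated as a matter of fact, or by a figure that can be calculated. The documents do not support that.

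- The dose-limiting transaminase rises occurred above 40 mg/day. This trial gives 20 mg/day.
- The remark on the leukemia patient, "this patient's lymphocyte count consistently rose during the week off therapy, then decreased once AT-101 was restarted", is reported with stable disease as evidence of activity. It is not an example of laboratory toxicity that reverses off drug.
- The troponin values that normalised within a week were judged not clinically significant, and the text does not tie recovery to stopping drug. Another patient's level normalised while AT-101 continued.
- The plasma half-life of about 4 hours describes clearance of drug, not recovery of enzymes or counts.
- The protocol gives neither the duration of laboratory abnormalities at this dose nor the share of grade 3 or higher toxicity that is laboratory-only. Any percentage missed would rest on invented inputs.

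Nor is the troponin schedule shown to be wrong: a draw directly after the last dose complies. The gap is that no latest day is stated.

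**Conclusion.** The point holds in a limited form. In continuing cycles started on time, scheduled hematology and chemistry fall 5 to 8 days after the last dose and never on a dosing day. Short-lived, silent laboratory toxicity can be missed, and the laboratory component of the 11.3 proportion and the 11.4 rate may be biased downward. The direction is certain if any such event is missed; the amount cannot be derived from the protocol. Clinical events, off-treatment tests and unscheduled tests are outside the problem.

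The 11.4 rule has little slack. Under the assumed 40% true rate, uncounted toxicity in 10% of affected patients takes the chance of review from 0.575 to 0.410 (two-sided bound) or from 0.726 to 0.575 (one-sided). This is an improvement worth making because it is cheap, not a flaw that invalidates the safety analysis.

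**What to change.** Run the existing hematology panel (footnote 9) and chemistry panel (footnote 10) on the blood draw already scheduled for cycle 1 week 2 (footnote 16), and count the results in the 11.3 and 11.4 rates. Every patient who completes one cycle will have passed that visit before the 11.4 assessment. The cost is an amendment to one table column and its footnotes and a few extra tubes, once each, in at most 56 patients. The reported toxicity rate may rise, and there may be more abnormal values to handle under 5.1 as it stands. One draw in week 2 will not catch events in week 3 or in later cycles, so it reduces the gap without closing it.

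If no draw is added, state alongside the 11.3 and 11.4 rates that scheduled laboratory data in continuing cycles come from the off-drug week and that transient on-drug abnormalities may be under-counted. The whole rate should not be labelled as toxicity present 5 to 8 days after dosing, because off-treatment and unscheduled tests fall outside that window.

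Separately, the sponsor should reconcile the pre-cycle placement of troponin with footnote 14 and section 4.3, which give no latest day, and the skip and hold rules in 5.1 with the schedule in 9.1. No clinical rule is proposed here.

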## **4.2 Treatment Requirements**

All eligible patients who consent to this study must have a baseline pretreatment MRI or CT scan. This scan must be done up to 14 days prior to the initiation of treatment. This MRI will be used for determining tumor response. An MRI (with bi-dimensional measurement) is preferred for evaluating tumor size. However, if the patient is unable to undergo MR (because of presence of a pacemaker, aneurysm clip or claustrophobia), CT scans will be performed consistently and used for analysis.

Patient enrollment and commencement of protocol therapy may begin as soon as is deemed medically appropriate. The patient will then receive AT-101 as described and receive a clinical assessment every 28 days (4 weeks or 1 cycle), with bi-dimensional scans performed before every odd treatment cycle (i.e. prior to cycles 1,3,5 etc). If during any scheduled MRI, patient has a Complete or Partial Response, MRI should be repeated prior to next cycle. Patients will then return to the every odd cycle schedule. This is required to confirm duration of response. All patients will be followed for survival.

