### **9.2.2 Recording of Adverse Events - ABTC AE Form**

- **Document on ABTC Adverse Event Form**
  - **Using AdEERS Application**
- 1) **CTCAE term (AE description) and grade:** The descriptions and grading scales found in the revised NCI Common Terminology Criteria for Adverse Events (CTCAE) version 4.0 will be utilized for AE reporting beginning January 1, 2011. All appropriate treatment areas should have access to a copy of the CTCAE version 4.0. A copy of the CTCAE version 4.0 can be downloaded from the CTEP web site (<http://ctep.cancer.gov>).
  - 2) The Investigator will monitor each patient closely for the development of adverse events and toxicities and record all such events on the ABTC AE Form. Each single sign or symptom must be reported separately. The DCTD/NCI Common Terminology Criteria for Adverse Events, CTCAE v.4.0 will be employed to record these toxicities beginning January 1, 2011. **A copy of the CTCAE version 4.0 can be downloaded from the CTEP home page (<http://ctep.cancer.gov>). All appropriate treatment areas should have access to a copy of the CTCAE version 4.0. You must use one of the CTCAE criteria to define your event.**
  - 3) Adverse events not included in the CTCAE v.4.0 should be reported and graded under the Other adverse event within the appropriate category and grade 1 to 5 according to the general grade definitions, mild, moderate, severe, life-threatening, fatal or disabling, as provided in the CTCAE or the CTCAE Manual. For new adverse events, the investigator may use the Adverse Event Module, Appendix I of the CTCAE, v.4.0. Also, new adverse events may be submitted to the CTEP Help Desk for annual evaluation by the CTCAE Change Management Committee.
  - 4) Abnormal lab results which are graded by NCI CTCAE v.4.0 will be recorded on ABTC Laboratory Checklist, along with documented attribution, not on AE form. However, if an action was conducted due to this abnormality (e.g. RBC transfusion due to low Hgb) this would be recorded on the AE form also.

All adverse events should be followed up in accordance with good medical practice. Abnormalities of laboratory events which, in the opinion of the Investigator, constitute adverse events (even if not serious) should be followed.

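### Footnote 6 of section 9.1 clearly requires weight only before odd cycles, so weight loss tabulated by cycle can be graded late or without a measured weight

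*Protocol*

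**What the plan says.** The protocol's table of required observations (section 9.1) schedules vital signs at baseline, before odd cycles, before even cycles and at off treatment; all four cells cite footnote 6. That footnote lists temperature, blood pressure, respiratory rate and heart rate, and adds in parentheses that "weight only needs to be obtained every odd cycle". The off-treatment cell also cites footnote 7: "Repeat only if > 3 calendar days since last eval/test". Neither footnote says whether weight is included at that visit.

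The same table places "AE Evaluation" before every odd and every even cycle and at off treatment, with the instruction to "Collect for at least 30 days post last dose of AT-101". History, physical and neurological examination follow the same visits and are also done at baseline. Section 4.2 has patients "receive a clinical assessment every 28 days (4 weeks or 1 cycle"), and section 9.2.2 states that "Each single sign or symptom must be reported separately".

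Section 9.3 lists weight loss as possibly related to AT-101, in the column for events seen in at most 20% of patients, and places it on the expected (ASAEL) list. The Appendix I worksheet carries a course number and a pre-printed weight loss row with grades 1 to 3. On analysis, section 11.3, item 1, says: "The frequency of different type toxicities will be tabulated by each cycle of the treatment".

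**The concern.** Weight loss is graded most soundly from serial weights. The protocol asks for a grade by course and a tabulation by cycle, but clearly requires a weight only at every second cycle boundary. At the end of an odd cycle, site staff may have no current weight on which to base a grade.

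Two further places lean on toxicity being known after a single cycle. Section 4.1 applies its criteria for non-hematologic recovery before every cycle, cycle 2 included. The safety look in section 11.4 takes place once 25 patients have had at least one cycle.

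Under section 9.2, patients are evaluable for toxicity after one dose. Early stoppers therefore count in the toxicity denominator even if no weight after baseline was clearly required of them. They may include patients with gastrointestinal toxicity, in whom weight loss is plausible. At stake is how well one listed adverse event is ascertained and dated, within the first secondary objective.

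**Working it through.** The plan states no figure on this point, so there is none to reproduce. The check is mainly a reading of the schedule.

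**Step 1. When a weight is clearly required.** Cycles last 28 days (section 4.1). Without delays, cycle 2 starts at week 4, cycle 3 at week 8, cycle 4 at week 12 and cycle 5 at week 16.

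| Visit | Vital signs | History and physical | AE evaluation | Weight |
|---|---|---|---|---|
| Baseline (before cycle 1) | yes | yes | – | yes |
| Before cycle 2, week 4 | yes | yes | yes | not required |
| Before cycle 3, week 8 | yes | yes | yes | yes |
| Before cycle 4, week 12 | yes | yes | yes | not required |
| Before cycle 5, week 16 | yes | yes | yes | yes |
| Off treatment | yes, subject to footnote 7 | yes, subject to footnote 7 | yes, subject to footnote 7 | unclear |

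The first clearly required post-baseline weight is at 2 × 28 = 56 days, or week 8.

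**Step 2. What this does to placement by cycle.**
- Loss arising in cycle 2, 4 or 6 is measured at the end of that same cycle and is placed correctly.
- Loss arising in cycle 1, 3 or 5 reaches a required weight one cycle later. From the required weights alone it cannot be separated from loss in the following cycle. It is placed correctly only if the AE evaluation before the even cycle records it.

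**Step 3. Patients who stop before cycle 3.** Their only clearly required weight is the baseline one. Whether the off-treatment visit adds another depends on how a site reads footnote 6.

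**Step 4. A rough guide to how many stop before week 8.** Inputs: 56 patients (section 3.1); 6-month progression-free survival (PFS) of about 15%, which section 11.4 gives for this population without effective treatment; 6 months taken as 26 weeks (section 11.3). Two assumptions are not in the document: time on treatment is exponential, and treatment ends only at progression or death. The share off treatment before week 8 is then 1 − PFS6^(8/26).

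| 6-month PFS | Share before week 8 | Of 56 patients |
|---|---|---|
| 10% (assumed) | 1 − 0.10^(8/26) = 0.508 | 28.4 |
| 15% (section 11.4) | 1 − 0.15^(8/26) = 0.442 | 24.8 |
| 20% (assumed) | 1 − 0.20^(8/26) = 0.391 | 21.9 |
| 25% (assumed) | 1 − 0.25^(8/26) = 0.347 | 19.4 |

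The range of interest is 35% to 44%, or about 19 to 25 of 56, for 6-month PFS from 25% down to 15%. It is neither an upper nor a lower limit. It counts progression found on the scan before cycle 3, the first scheduled scan after baseline, which belongs to a visit where weight is due. It leaves out stops for toxicity or refusal, which section 10.0 allows and which PFS does not capture.

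**The case against.** The strongest case on the other side is that footnote 6 sets a minimum and forbids nothing. AE evaluation and physical examination take place before every cycle and at off treatment, AEs are followed for at least 30 days after the last dose, and the worksheet prompts for weight loss with an event date and a course number. Nothing in the document says that weight loss enters the section 11.3 table only through a scheduled weight. Performance status and MRI are likewise scheduled before odd but not even cycles, so the lighter schedule may be deliberate. The dose is flat, so weight has no part in calculating it, and the worksheet gives weight loss no grade 4 or 5.

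Much of this stands, and it rules out several stronger readings that a reader might draw:

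- That weight loss goes unmeasured in early stoppers. The document does not say so: weight at off treatment is unclear rather than excluded, and AE evaluation can record the event.
- That all other weight loss is put in the wrong cycle, or that the by-cycle table can show it only in even cycles. Loss arising in even cycles is placed correctly, and odd-cycle loss picked up at the next AE evaluation is too.
- That the toxicity objective as a whole is distorted. The nausea, vomiting, diarrhea and anorexia that might accompany weight loss do not depend on a weight and are assessed every cycle.

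What the objection does not remove is the missing basis for grading. AE evaluation may elicit a report of weight loss, but an objective grade needs a weight, and the one footnote that mentions weight makes it optional before even cycles. The doubt over the off-treatment cell is itself a reason to edit, since sites may read it differently.

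**Conclusion.** The concern holds in a limited form. Section 9.1 clearly requires weight only before odd cycles and is unclear at off treatment, while Appendix I grades weight loss by course and section 11.3 tabulates toxicity by cycle. Odd-cycle loss can be graded late or without a measured basis unless the AE evaluation catches it, and a patient who stops before about week 8 has no clearly required post-baseline weight.

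The effect is limited to the frequency and cycle timing of one adverse event. Overall survival, the 52 required events and the sample size of 56 do not depend on it. The number of early stoppers without a weight cannot be fixed from the document; the 35% to 44% rests on an assumed exponential form and on PFS standing in for time on treatment, and is not a bound. The case for acting is that better ascertainment of a listed, expected event costs almost nothing, not that a large bias has been shown.

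**What to change.** In footnote 6 of section 9.1, delete the parenthesis and add weight to the listed vital signs, so that it is taken at baseline, before each odd and each even cycle, and at off treatment. This also settles the off-treatment cell; footnote 7 would continue to govern repeats there. In section 11.3, item 1, state that weight loss is tabulated by the cycle just completed.

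The cost is two short text edits and one extra routine weighing at visits where vital signs and a physical examination are already scheduled. No visit or analysis is added, and dosing and clinical management rules are unchanged.
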